## Sample size and statistical analysis

As the primary aim of the prospective trial is exploratory, no sample size calculation is performed. The statistical tests will be performed in the SPSS software program (version 13.0, SPSS, Chicago, IL, USA). A two-sided *P* value less than 0.05 will be considered statistically significant. Descriptive statistics will be used for baseline demographic and clinical characteristics of participants (i.e., mean and standard deviation for continuous variables, proportions for categorical variables). A χ^2^ test or Fisher’s exact test will be applied for categorical variables. Student’s *t* test or the Mann-Whitney *U* test will be used for continuous variables. Kaplan-Meier curves and log-rank analysis will be used to compare the differences in DFS and OS among the three parallel groups.

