## Safety and adverse events monitoring

An independent data and safety monitoring board organized by oncologists, gastrointestinal surgeons, and statisticians is responsible for overseeing the progress and safety of the study, including adverse events, morbidity, and drop-outs. All adverse events will be evaluated for severity. Any serious adverse events such as death, disability, and prolonged hospitalization will be recorded on the CRF and reported to the board and the Biological and Medical Ethics Committee of West China Hospital within 24 h. If the number of serious adverse events related to treatment is more than in our own database or as reported by other authors, patient enrollment will be terminated immediately and the Medical Ethics Committee will reassess the safety of the trial. The schedule of study visits and follow-up is shown in Table 1.

**Table 1 Tab1:** Perioperative outcome parameters and schedule of study visits and follow-up

Measures	Preoperative	Intraoperative	Daily in-hospital study visit					Follow-up												
			POD 1	POD 2	POD 3	POD 4	POD 5	M1	M3	M6	M9	M12	M15	M18	M21	M24	M27	M30	M33	M36
Minimally invasive evaluation		X																		
Quality of specimens		X																		
VAS score			X		X		X													
Inflammatory parameters	X		X		X		X													
Short-term recovery			X	X	X	X	X													
Physcial examination	X							X	X	X	X	X	X	X	X	X		X		X
Tumor marker	X							X	X	X	X	X	X	X	X	X		X		X
Abdominal and pelvic CT scan	X									X		X		X		X		X		X
Colonoscopy	X											X				X				X
Adverse event		X	X	X	X	X	X	X	X	X	X	X	X	X	X	X	X	X	X	X

Preoperative study visits will be scheduled within 7 days before surgery

Minimally invasive evaluation includes operation time, blood loss, intraoperative complication, and incision length

Inflammatory parameters including procalcitonin (PCT), C-reactive protein (CRP), and interleukin (IL)-6 will be measured at 24 h, 72 h, and 120 h postoperatively

Short-term recovery including time to first flatus, liquid diet, and duration of hospital stay will be recorded daily in-hospital

Colonoscopy will be performed at 1 year after surgery and will be repeated at 3 years if no lesions are found

Tumor marker includes carcinoembryonic antigen (CEA) and carbohydrate antigen 19-9 (CA 19-9)

*CT* computed tomography, *M* Month, *POD* postoperative day, *VAS* visual analogue scale

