### Peritoneal wash collection

Peritoneal washes will also be collected at two different time points during the operative period. At the beginning of each operation, 100 ml saline will be introduced into the hepatorenal recess and the Douglas cavity and aspirated after gentle stirring. After complete mobilization of the cancer-bearing segment, another 100-ml peritoneal wash will be aspirated after gentle stirring. Each peritoneal wash will be used for RNA extraction. After the peritoneal washes are centrifuged for 10 min at 1000 × g, cells will be collected and rinsed with phosphate-buffered saline (PBS), dissolved in TRIzol RNA extraction buffer (Invitrogen, Carlsbad, CA, USA), and stored at –80 °C.

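### The named group comparisons are all unadjusted although baseline values are collected for some outcomes: the tests are valid, but precision that costs almost nothing is left unused

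*Protocol article*

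**What the plan says.** The section on sample size and statistical analysis gives baseline variables a descriptive role only. It then names the tests. For continuous outcomes, Student's t or the Mann-Whitney U "test will be used for continuous variables". For proportions, a chi-square or Fisher's "exact test will be applied for categorical variables". For survival, Kaplan-Meier curves and "log-rank analysis will be used to compare the differences in DFS and OS among the three parallel groups". No regression model, covariate or stratified test appears. The study design section describes allocation as 1:1:1 from a central list and names no stratification factor. On size, the article states: "As the primary aim of the prospective trial is exploratory, no sample size calculation is performed".

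Elsewhere the article describes three baseline measurements:

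- **Peritoneal wash.** "At the beginning of each operation, 100 ml saline will be introduced into the hepatorenal recess and the Douglas cavity". A second wash follows mobilisation of the tumour-bearing bowel. RT-PCR detection of shed tumour cells is listed under the primary outcomes.
- **Inflammatory markers.** The Table 1 row is marked in the preoperative column. The footnote begins "Inflammatory parameters including procalcitonin (PCT), C-reactive protein (CRP), and interleukin (IL)-6 will be measured" and then lists only 24, 72 and 120 h after surgery, as does the secondary outcomes section.
- **Clinical stage.** Eligibility requires it and allows cT1 to cT4a and N0 to N2a.

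**The concern.** When an outcome has a pre-treatment value of the same quantity, a comparison that ignores it carries between-patient variation that could be removed. The wash is the clearest case. The trial takes one sample before and one after mobilisation to ask whether technique affects shedding, but the statistical section does not say how the first sample enters the analysis. A two-sample test on the second wash ignores cells that were already present. A test on the difference between washes uses the first sample, but inefficiently when the two are weakly correlated.

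The same reasoning applies to the postoperative markers and, less strongly, to DFS and OS, where clinical stage is known before surgery. With no calculated sample size, there is no assurance that precision is ample. At stake are wider confidence intervals and lower power than the collected data could give. The type I error rate is not at stake.

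**Working it through.** The plan gives no sample size, effect size, SD or power, so there is no figure of its own to reproduce. What follows illustrates the size of the gain.

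**Inputs.** From the article: two-sided 5% level, 1:1:1 allocation, unadjusted tests. Assumed: a standardised difference of 0.5 between two arms, 80% power, and a baseline-outcome correlation ρ from 0.1 to 0.7.

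**Formulae**, relative to the variance of the raw outcome, with equal variances at both times:

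- unadjusted: 1
- change from baseline: 2 − 2ρ = 2(1 − ρ)
- baseline-adjusted (ANCOVA): 1 − ρ², equivalent to multiplying the sample by 1/(1 − ρ²)

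Unadjusted sample size per arm: 2(1.960 + 0.842)²/0.5² = 62.8, so 63. The adjusted size replaces the SD of 1 by √(1 − ρ²).

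| ρ (assumed) | Change-score variance | Adjusted variance | Variance cut | Equivalent sample | n per arm, 80% power | Power at 63 per arm |
|---|---|---|---|---|---|---|
| 0 | 2.0 | 1.00 | 0% | 1.00 | 63 | 80.1% |
| 0.1 | 1.8 | 0.99 | 1% | 1.01 | 63 | 80.5% |
| 0.3 | 1.4 | 0.91 | 9% | 1.10 | 58 | 83.7% |
| 0.5 | 1.0 | 0.75 | 25% | 1.33 | 48 | 90.0% |
| 0.7 | 0.6 | 0.51 | 49% | 1.96 | 33 | 97.6% |

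A change score has more variance than ignoring baseline whenever ρ is below 0.5. The adjusted analysis is never worse than either, apart from one degree of freedom.

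**Simulation check** (63 per arm, 4,000 runs per setting). Power of the t test against ANCOVA was 79.0% v 79.2% at ρ = 0.1, 79.8% v 83.1% at 0.3, 79.4% v 89.4% at 0.5 and 78.6% v 96.8% at 0.7. Type I error lay between 0.044 and 0.057 for both methods. The unadjusted test is therefore valid, and only power differs.

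**Survival.** The assumptions are a treatment hazard ratio of 0.5 and a stage hazard ratio of 3 to 5. In 4,000 replicates per setting, stratifying the log-rank test by stage raised power from 0.386 to 0.397 and from 0.468 to 0.514 at 100 per arm, and from 0.669 to 0.686 and from 0.765 to 0.805 at 200 per arm. The gain is about 1 to 5 percentage points.

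**Which outcomes can benefit.** The second wash has a usable baseline: the first wash comes at the start of surgery, before mobilisation. The markers have one if the Table 1 mark is correct. The blood RT-PCR does not, because the first portal (SMV) and peripheral samples are drawn only after the distal SMV has been exposed, by which time operative steps that differ between arms have taken place. Pain has no preoperative mark in Table 1, and operative and specimen measures have no baseline by nature.

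**The case against.** The strongest objection is that covariates and stratified tests usually belong in a SAP, which is not shown, and that a condensed article naming simple valid tests has made no error. Much of this stands. The tests control type I error, no stratification factor is stated that would oblige adjustment, and the trial calls its aim exploratory. It does not dispose of the point, because the article goes beyond silence: it names the tests, and better ones are available from the same data.

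Four stronger readings are tempting, and the documents do not support them.

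- A reader might infer that every analysis in the trial will be unadjusted. Only the comparisons named in the statistical section are known to be.
- A reader might infer that the baseline values are strong predictors. No correlation or prognostic strength is given, and at ρ of 0.3 or less the variance gain is at most 9%.
- A reader might infer that a t test is forced on the right-skewed RT-PCR ratio. The same sentence offers the rank-based Mann-Whitney test.
- A reader might infer that chance imbalance in stage could be mistaken for a DFS effect. Such imbalance is already within the log-rank test's error rate. It also shrinks with size: if 40% are node-positive (assumed), two arms differ by 10 points or more with probability 0.358 at 50 per arm, 0.170 at 100 and 0.046 at 200.

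**Conclusion.** The point holds as a missed efficiency gain. For the second wash and the inflammatory markers, the stated tests give up a variance reduction of ρ², which runs from 1% to 49% over the assumed range of 0.1 to 0.7. Nothing in the documents narrows that range. For DFS and OS the expected gain is a few percentage points of power, and only under large assumed treatment and stage effects. Outcomes without a baseline value are unaffected. This is an improvement worth making because it is nearly free. It does not correct an invalid analysis.

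**What to change.** Amend the statistical section as follows, or point to the SAP if it already does this:

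1. **Peritoneal wash RT-PCR.** Make the main comparison a linear model for the post-mobilisation value on the log (delta-Ct) scale, with arm and the first-wash value as terms. Prespecify how undetected values are handled. The discussion cites a study that found CEA products in only one of eighteen conventionally operated patients, so non-detection may be common.
2. **PCT, CRP and IL-6.** Analyse on the log scale over 24, 72 and 120 h, adjusted for the preoperative value. First reconcile the preoperative mark in Table 1 with the footnote and the secondary outcomes section, which list postoperative times only.
3. **DFS and OS.** Use a log-rank test and Cox model stratified by a simple prespecified clinical stage grouping, for example cN0 versus cN+. Finer groups could be sparse when the trial size is unknown. Report the stratified hazard ratio as conditional on stage.
4. **Blood samples.** State that the first SMV and peripheral samples are not used as baseline covariates.
5. Keep the unadjusted tests as supportive analyses.

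The cost is wording. The two washes and clinical stage are already collected. The preoperative markers need no new data if the Table 1 mark reflects practice.

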## Interventions

An experienced colorectal surgeon with more than 400 successful laparoscopic colorectal resections every year will perform all procedures in this trial.

### Experiment intervention

After general anesthesia, the patient will be placed in the supine position with legs apart. The chief surgeon stands between the legs, and two assistants stand on the left side of the patient. The monitor is placed at the patient’s head. The positions of the chief surgeon, assistants and monitor are shown in Fig. 2a.

**Fig. 2 Fig2:**
[figure not shown]
Operative position and trocar positions for the experimental intervention group. **a** The operative position for HALS-CME. **b** The trocar placement for HALS-CME. Trocars A and B = 12 mm, trocar C = 5 mm

An initial 7-cm midline incision around the umbilicus will be made as the hand-assisted port and the Dextrus hand access device (Ethicon, USA) will be inserted through the umbilical incision. A 12-mm port (trocar A) in the left lower quadrant will be established as the surgeon’s dominant operation channel. In the upper left quadrant, one 12-mm port (trocar B) will be established to maintain a pneumoperitoneum of 12–15 mmHg, and the camera will be introduced through this port. Another 5-mm port (trocar C) slightly below the xiphoid will also be established as the assistant’s operation channel to retract the mesocolon and the stomach. The midline incision and trocars are shown in Fig. 2b.

With the space created by the Dextrus, the whole operation procedure will be divided into extracorporeal and intracorporeal stages. Under direct visualization, the greater omentum, transverse colon, and terminal ileum can be exposed extracorporeally through the hand-assisted port. First, the transverse colon will be dragged out and the right branch of the middle colic vessels will be divided; after that, the transverse colon will also be divided to the left of the main trunk of the middle colic vessels and returned to the abdominal cavity (Fig. 3a). Second, the distal ileum from 6 to 10 cm proximal to the ileocecal valve as the proximal margin of resection is divided (Fig. 3b). The terminal of the superior mesenteric vein (SMV) can then be easily identified by holding and stretching the stump of the distal superior mesenteric vessels (Fig. 3c). We generally create a window around the terminal SMV, and dissection along the left side of the SMV will proceed up towards the origin of the ileocolic pedicle, and the pedicle will be divided extracorporeally (Fig. 3d). The small bowel and mesentery will then be returned to abdominal cavity. The chief surgeon’s left hand is put into the abdominal cavity through the hand-assisted port which facilitates maintaining a pneumoperitoneum of 12–15 mmHg.

**Fig. 3 Fig3:**
[figure not shown]
The extracorporeal surgical procedure for the HALS-CME group. **a** The transverse colon is divided after the right branch of the middle colic artery ligation. **b** The distal ileum is divided. **c** The terminal of the SMV is identified. **d** Dissection along the left side of the SMV proceeds up towards the origin of ileocolic pedicle, and the pedicle is divided

In the intracoporeal stage, the principle of European CME and Japanese D3 lymphadenectomy will be followed when right colon resection with en-bloc lymphadenectomy is performed. The extent of the third tier lymph node (N3) dissection (D3) along the SMV is showed in Fig. 4a. The second operation stage under laparoscopy is described as follows:

**Fig. 4 Fig4:**
[figure not shown]
The intracorporeal surgical procedure for the HALS-CME group. **a** The extent of the D3 lymphadenectomy. **b** The neck of pancreas is exposed and middle colic vessels are divided. **c** The Henle’s trunk is identified and handled. **d** The mobilization of the tumor-bearing segment is performed from medial to lateral

When the transverse mesocolon and the middle colic vessels undergo retracted cephalad retraction, the inferior edge of the neck of pancreas will be identified as a landmark and destination for the following steps.In the first stage, the SMV has been identified and the ileocolic vessels have been divided; dissection is then continued along the left side of the SMV in a repeated unidirectonal/longitudinal manner until the neck of pancreas is exposed and the lesser omental bursa is entered. Meanwhile, the right colic artery and middle colic vessels will also be exposed and divided (Fig. 4b).After exposing the whole length of the neck of pancreas, identifying Henles’ trunk and the pancreaticoduodenal vein, the right colic vein is then divided (Fig. 4c).After completion of the D3 lymphadenectomy along the SMV, the greater omentum will be removed, and mobilization of the right colon mesentery from medial to lateral will be performed with the help of the hand (Fig. 4d).Finally, the specimen will be removed through the hand-assisted port, an end-to-side anastomosis will be fashioned, the mesenteric defect will be closed extracorporeally.

### Control intervention

In this trial, in order to adequately test the novel HALS-CME technique and balance baseline characteristics among groups, two control groups (laparoscopy CME (LAP-CME) and conventional laparoscopy (cLAP)) will be set up.

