## Methods and design

### Study design and setting

This is a single-center, open-label, noninferiority, randomized controlled trial undertaken at West China Hospital of Sichuan University (Chengdu, Sichuan, China), which performs 2000 colorectal cancer resections per year. The chief surgeon performs more than 400 laparoscopic-colorectal cancer resections per year. Participants will be randomly assigned to three parallel groups at a 1:1:1 ratio using a centralized randomization list. Patients assigned to the HALS-CME group will receive the hand-assisted laparoscopic surgery with CME, D3 lymphadenectomy, and total “no-touch” isolation technique (HALS-CME). Patients in the LAP-CME group will receive laparoscopic surgery with CME, D3 lymphadenectomy, and total “no-touch” isolation technique. Meanwhile, patients in cLAP group will receive conventional laparoscopic surgery with CME and D3 lymphadenectomy (Fig. 1). Blood samples and peritoneal washes will be collected from each participant during the operative procedure. Recruitment began on December 2015, and the trial is expected to proceed for 3 years.

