## Outcome measures

### Primary outcomes

The primary endpoints are safety, efficacy, and being oncologically clear. Perioperative morbidity will be divided into intraoperative morbidity observed during the operation and postoperative morbidity observed during the hospital stay and within 30 days at the outpatient clinic. Postoperative morbidity will be assessed according to the Clavien-Dindo classification. Real-time polymerase chain reaction (RT-PCR) will be used to test whether the novel total “no-touch” isolation technique could potentially reduce tumor cells shedding into the portal circulation, peripheral circulation and peritoneal cavity. Other primary outcomes include 3-year disease-free survival (DFS), progression-free survival (PFS), overall survival (OS), and recurrence pattern (local recurrence, metastasis).

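### Baseline balance is given as a reason for having two control groups, which extra arms cannot provide; stage is better handled by stratifying the DFS and OS log-rank test

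*Protocol article*

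**What the plan says.** In the protocol article, Control intervention, the two comparator arms (LAP-CME and cLAP) are set up "in order to adequately test the novel HALS-CME technique and balance baseline characteristics among groups, two control groups". Two reasons are given: an adequate test of the new technique, and balance.

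On allocation, Study design and setting says "Participants will be randomly assigned to three parallel groups at a 1:1:1 ratio using a centralized randomization list". No blocking or stratification factor is named. The list is not described as simple or unstratified either.

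Inclusion criteria admit clinical stages cT1 to cT4a and N0 to N2a, without metastases, so node-negative and node-positive patients enter together.

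Under Primary outcomes, "Other primary outcomes include 3-year disease-free survival (DFS), progression-free survival (PFS), overall survival (OS), and recurrence pattern". For analysis, Sample size and statistical analysis says "Kaplan-Meier curves and log-rank analysis will be used to compare the differences in DFS and OS among the three parallel groups". No stratification or covariate is named there. The same section says "As the primary aim of the prospective trial is exploratory, no sample size calculation is performed", and no arm size or total appears elsewhere in the article.

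**The concern.** The article offers a mechanism for baseline balance that does not work. Randomization balances in expectation. Stratified allocation or an adjusted analysis deals with named factors. Adding a comparator arm does neither.

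A reader who accepts the sentence may think stage comparability has been secured by design, and so see no need for it in the analysis. The eligible stage range is wide and survival outcomes are primary. If one arm happens to hold more node-positive patients, an unstratified log-rank test folds that difference into the estimated contrast between techniques. The article's own Discussion shows why this matters for interpretation: it notes that an earlier retrospective no-touch benefit may have reflected more extended resection in that group.

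**Working it through.** **1. What the second control arm contributes.** Setting the arm descriptions in Interventions side by side:

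| Contrast | What differs |
|---|---|
| HALS-CME v LAP-CME | hand port, with its extracorporeal stage; both divide the bowel before mobilizing the tumor segment |
| LAP-CME v cLAP | whether the bowel is divided first (no-touch) or after the segment is brought out; both fully laparoscopic |
| HALS-CME v cLAP | both together |

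The second control therefore separates two components that a single control would confound. That is a good reason for it, and it has nothing to do with baseline balance.

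**2. Effect of a third arm on balance.** With n per arm and a true node-positive share p, the SD of the difference between two arms is sqrt(2p(1−p)/n). Splitting a fixed total N three ways instead of two changes n from N/2 to N/3, so the SD is multiplied by sqrt((N/2)/(N/3)) = sqrt(1.5) = 1.22. With p = 0.40, the chance that one given pair differs by at least 10 points is:

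| Total | Two arms | Three arms |
|---|---|---|
| 90 | 33% | 51% |
| 150 | 21% | 36% |
| 300 | 9% | 17% |

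The fixed total is an assumption; the article sets none.

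**3. Size of chance imbalance by arm size.** There is no planned figure to reproduce. Assumptions not in the documents: p = 0.40, and independent binomial counts in each arm (simple randomization). At 40 per arm the SD is sqrt(2 × 0.4 × 0.6/40) = 0.110, so 10 points is 0.10/0.110 = 0.9 SD. At 200 per arm it is sqrt(0.48/200) = 0.049, so 10 points is 2.0 SD. Summing the binomial probabilities for a difference of at least 10 points:

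| Per arm | One given pair | HALS-CME v at least one control | Any of the three pairs |
|---|---|---|---|
| 40 | 42% | 64% | 70% |
| 60 | 31% | 49% | 56% |
| 100 | 17% | 29% | 36% |
| 150 | 9% | 15% | 20% |
| 200 | 5% | 8% | 11% |

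Varying p from 0.30 to 0.50 moves the one-pair chance only to 3–5% at 200 per arm and to 60–64% at 20 per arm. Arm size drives the answer, not p.

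**4. What an imbalance does to DFS.** Assume 3-year DFS differs by 15 to 25 points between N0 and N-positive patients (again not in the documents). A 10-point difference in stage mix then moves the DFS contrast by 0.10 × 15 = 1.5 to 0.10 × 25 = 2.5 points.

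**5. What stratifying the log-rank buys.** In an illustrative simulation, power rose from about 60% unstratified to about 63% stratified by N status, with type I error near 5% for both. I repeated this for two arms with 40% node-positive, 3-year DFS of 85% in N0 and 65% in N-positive, and complete 3-year follow-up. Power went from 50% to 52% (100 per arm, hazard ratio 0.5) and from 58% to 59% (200 per arm, hazard ratio 0.6); type I error was 4.7–5.1%. The gain is small, and the unstratified test is valid.

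**The case against.** The strongest reply is that deleting the clause changes nothing the trial does. No endpoint, test or allocation step depends on it, and the three-arm design is sound for the article's other stated reason. That stands, and it is why the point is minor.

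A reader might infer several stronger claims. The documents do not support them.

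- *The list is unstratified, so stage is left to chance.* The article says only that the list is centralized and 1:1:1. A condensed article commonly leaves blocking and stratification to the full protocol, and covariate adjustment to the SAP. Their absence here proves nothing.
- *The arms are small.* No sample size is given. The center reports 2000 colorectal cancer resections a year and expects the trial to run for 3 years; the share eligible is unknown. At 200 per arm the problem nearly disappears.
- *An important imbalance against HALS-CME is likely.* On the assumptions above, a 10-point difference from at least one control is more likely than not at 40 per arm, but not at 60 or more.
- *Imbalance would create a false technique effect.* Chance imbalance under randomization is already reflected in the type I error of the unadjusted test. It adds noise and makes a single result harder to read.
- *The shedding comparison has no protection.* The first peritoneal wash is taken at the start of the operation, so that compartment has a within-patient baseline. The first blood sample comes only after the distal SMV is exposed, so it is a less clean baseline; that does not establish a stage problem.

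Stratified blocks also have a cost in an open-label, single-center trial with one operating surgeon: many small strata make assignments easier to predict.

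**Conclusion.** The statement in Control intervention is wrong: two control arms cannot balance baseline characteristics, and at a fixed total the extra arm widens chance differences by a factor of 1.22. This is an error of rationale, not a demonstrated fault in the randomization or the comparisons.

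The practical consequence is limited. With a wide stage range and no stratification named for the DFS and OS log-rank, any chance stage difference enters that comparison unadjusted. The loss is in precision and interpretability. The probability of a 10-point difference for a given pair runs from about 42% at 40 per arm to 5% at 200, assuming 40% node-positive and simple randomization. The article gives neither the arm size nor the node-positive share, so no single figure can be claimed.

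**What to change.** 1. In Control intervention, replace the balance clause with the actual role of the two controls: HALS-CME v LAP-CME for hand assistance, and LAP-CME v cLAP for the no-touch sequence. This costs one sentence.

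2. In Sample size and statistical analysis, make the DFS and OS log-rank stratified by preoperative clinical N status (N0 v N1–2a). Add cT only if the resulting strata are not sparse. Fix this before outcomes are examined by group. Clinical stage is already an eligibility item, so no new data are needed and patients already randomized are covered. If the SAP already stratifies, it is enough to state that here. The costs are a short amendment and some lost information if strata become thin. The change does not reach the shedding outcomes.

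3. Optionally, stratify the remaining allocation by N status. This needs a new central list and stage entry before the assignment is released, it makes assignments somewhat more predictable, and it leaves earlier patients as they were allocated. It should not be presented as repairing a demonstrated fault.
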